## Abstract

**Introduction:**

An estimated 10% of women experience severe, chronic pelvic girdle pain post partum. This has significant physical, psychological and socioeconomic consequences. Typically, such pain is recalcitrant to conservative management; hence the need to identify effective management strategies. Customised Dynamic Elastomeric Fabric Orthoses may be an option to address this gap; designed to improve pain by providing support while optimising movement and function. Currently, no studies have evaluated the clinical and cost-effectiveness, or acceptability of these customised orthoses in postpartum women.

**Methods and analysis:**

EMaPP is a pragmatic, multicentre randomised controlled feasibility trial with an embedded qualitative study and economic evaluation. Sixty participants with pregnancy-related severe pelvic girdle pain >3 months post partum will be recruited. Participants will be randomly allocated in a 1:1 ratio (stratified by centre and presence/absence of lumbo-pelvic pain pre pregnancy) to receive either standard care (standardised information and exercise) or intervention (orthosis plus standard care). All participants will be asked to complete a battery of self-report questionnaires (including pain, function, health-related quality of life and health and social care resource use), via a web-based application at baseline, 12 weeks and 24 weeks. Pain levels and medication usage will be reported fortnightly. Feasibility and acceptability of the trial procedures will be determined in terms of recruitment and retention rates, data completion rates and intervention adherence. Five clinicians and 10 participants will be interviewed to explore their experiences of the trial procedures and receiving the intervention.

**Ethics and dissemination:**

This study was approved by: National Research Ethics Scheme (NRES Committee Health and Care Research Wales Research Ethics Committee (21/WM/0155) and University of Plymouth Faculty of Health Research Ethics and Integrity Committee (ref:2966). Results will be made available to participants, the funders, staff, general public and other researchers through a range of mechanisms.

**Trial status:**

Currently recruiting.

**Trial registration number:**

ISRCTN67232113.

Strengths and limitations of this studyEMaPP is the first multicentre randomised controlled feasibility trial assessing the feasibility and acceptability trial procedures, comparing the delivery of a novel pelvic orthosis plus standard care with standard care alone in women experiencing severe pelvic girdle pain post partum.All trial procedures and outcome measures are undertaken virtually, examining the acceptability of this approach.EMaPP data collection has accounted for the worst and average pain with the Numerical Rating of Pain Scale (in full), collected fortnightly, capturing the variability and the cyclical nature of pain experienced by participants.The trial includes an embedded qualitative element investigating acceptability of the intervention and trial procedures, with purposive sampling to capture a diversity of views from the participants and clinicians.A limitation is that adherence to exercise is not systematically captured.

## Introduction

An estimated 70% of women experience pelvic girdle pain (PGP) during pregnancy,^1^ with approximately 10% of these experiencing this for longer than 3 months post partum. For some this pain is severe and long lasting, with reports of pain for more than a decade post partum.^2–4^ This has significant physical, psychological and socioeconomic consequences. Often everyday activities are affected such as moving in bed, walking, driving, breast feeding (due to discomfort and the effect of analgesia in breast milk), continence (due to associated pelvic floor dysfunction) and safely caring for the child and siblings, especially as the child becomes more mobile.^5^ The emotional impacts of ‘living with enduring pain’, include anger and frustration and feelings of ‘being a burden’,^6^ with related abuse of analgesics highlighted.^7 8^ Work absenteeism contributes significantly to the economic consequences.

Despite such wide-ranging impacts, symptoms can be overlooked or dismissed by health professionals believing the pain will naturally resolve.^2 9^ However, severe long-lasting pain is often recalcitrant to usual management,^10 11^ and can ultimately require invasive and expensive fluoroscopy guided injections and surgical procedures (ablation and fusion). There is an urgent need for effective strategies to address this personal and societal burden. In particular, guidance is needed for the extended postpartum phase since all current guidance relates to pain during pregnancy and up to 8 weeks post partum.^12^ In light of this, National Health Service (NHS) England has committed to improving access to postnatal physiotherapy.^13^

Pelvic orthoses are one option to manage this condition having support from European guidelines,^14^ and the Royal College of Obstetricians and Gynaecologists.^15^ These are externally worn devices designed to increase pelvic joint stability, musculoskeletal alignment and sensory input to optimise muscle control, pain and function.^16^ There is currently a wide range of ‘off the shelf’ pelvic orthoses available, however they have been shown to be of mixed benefit and often ineffective when pain is severe.^17^ Furthermore, women report wear-time issues due to discomfort, lack of ease of use, reduced aesthetics and impact on movement.^8^ Sufficient wear time is however crucial for orthotics as benefits gained are dependent on this.

A novel customised Dynamic Elastomeric Fabric Orthosis (DEFO) for people with PGP has been designed, (DM Orthotics’, https://www.dmorthotics.com) to address these issues. This pelvic orthosis differs markedly in the design, material and compression grades to ‘off the shelf’ pelvic orthoses. Their use has been previously assessed; during pregnancy, through a randomised controlled trial (RCT), finding that they significantly improved pain over and above the traditional rigid belt;^18^ and in a replicated case series of group of eight women experiencing postpartum PGP, identifying an improvement in pain, function and quality of life.^19^ Both studies indicated the pelvic DEFOs were acceptable to wear with regard to wear time, comfort and aesthetics. These studies together indicate a potentially effective new treatment option to managing this difficult to treat condition in the postpartum period. Further evidence is required to establish the clinical and cost-effectiveness of this novel intervention in women experiencing persistent severe PGP following pregnancy. Before considering a definitive trial, the feasibility of running such a trial needs to be tested.

### Aims and objectives

The primary aim is to assess the feasibility and acceptability of the trial procedures comparing the delivery of a novel pelvic orthosis plus standard care with standard care alone in women experiencing severe, chronic PGP post partum.

The trial objectives are to gain operational experience and gather high-quality data to inform the conduct and design of an anticipated definitive RCT and cost-effectiveness analysis, including the most appropriate primary and secondary outcome measures, the most effective recruitment methods and to inform the sample size calculation of the future trial.

## Methods

### Trial design

The EMaPP trial is an assessor blinded, pragmatic, randomised controlled feasibility trial comparing standard care (standardised advice and exercises) to standard care in addition to a customised pelvic orthosis, with an embedded qualitative study. A Consolidated Standards of Reporting Trials (CONSORT) study flowchart outlines the participant pathway through the trial (figure 1). The study started in March 2021 and ends in June 2023.

**Figure 1 F1:**
[figure not shown]
Trial flow chart. CRN, Clinical Research Network; DEFO, Dynamic Elastomeric Fabric Orthosis; NRPS, Numerical Rating of Pain Scale; POGP, Pelvic, Obstetric & Gynaecological Physiotherapy.

### Study settings

The three study sites are based in three geographical regions of England: Devon, West Yorkshire and Buckinghamshire. The interventions are delivered in primary or secondary care subject to local practices.

The trial undertakes a remote, distance-based approach to its delivery at all stages.

Telephone and virtual screening.Interventions delivered via videoconferencing by NHS physiotherapy services using locally approved software.

To prevent digital exclusion, face-to-face intervention will be delivered at a local healthcare establishment when required.

### Eligibility criteria

The study population will comprise women with postpartum PGP, based on the eligibility criteria outlined in table 1.

**Table 1 T1:** EMaPP study inclusion and exclusion criteria

Inclusion criteria	Exclusion criteria
Aged ≥18 years.	Known allergy to Lycra.
Able and willing to provide informed consent.	Currently pregnant.
Self-report persistent PGP (for a minimum of 3 months post partum).	Currently wearing a catheter.
Self-reported severe PGP (causing walking or stair climbing to be bothersome).	Self-reported history of pathologies causative of lumbo-pelvic pain (eg, infection, trauma, cancer).
Diagnosis of PGP in line with European guidelines; defined as pain between the posterior iliac crest and inferior gluteal fold, particularly in the sacroiliac joint vicinity, that may radiate to the posterior thigh and occur in conjunction with or separately in the symphysis pubis,^14^ captured using the pain referral map.	Participating in concurrent interventional research which may overburden the patient or confound data collection.
Scoring positively with at least one anterior PGP test and two tests for posterior PGP or two positive tests for posterior PGP^39^ (figure 3).	Participants unable to understand verbal and/or written English adequate to complete the trial procedures/self-report questionnaires. Assistance from a friend/family member for translation purposes is acceptable.
The PGP must have started or been aggravated during pregnancy, as determined by self-report.	

PGP, pelvic girdle pain.

**Figure 2 F2:**
[figure not shown]
Customised pelvic support shorts (Dynamic Elastomeric Fabric Orthosis).

### Participant recruitment, identification and screening

A multifaceted recruitment approach will be undertaken as follows:

Nationally, social media will be used to promote the trial via a various sites including: Mumsnet, Facebook and Twitter pages of the pelvic, obstetric and gynaecological physiotherapy special interest group, National Maternity Voices, National Childbirth Trusts and the dedicated study website (https://www.plymouth.ac.uk/research/emapp-trial).

Locally, recruitment will occur via: the Clinical Research Networks who will undertake selected General Practitioner (GP) database searches; caseloads of physiotherapists working within musculoskeletal, women’s health services of the recruiting sites; posters in relevant outpatient clinics/ waiting areas of participating sites; local patient and public involvement and engagement (PPIE) groups and hospital social media accounts.

The trial will use a dedicated email address, included on all promotional material along with a QR code, to direct interested parties to further information on the trial website. The trial website contains a downloadable participant information sheet (PIS) and reply slip.

All interested participants, and those on databases or caseloads who are deemed potentially eligible, will be sent a trial information pack containing: PIS; details of the ethically approved study sites; and a reply slip to indicate their interest and confirm they feel they are eligible.

### Eligibility screening process

Eligibility screening will occur via a two-stage process. On receipt of the completed reply form a telephone screen (stage 1) will be undertaken using a pre-formatted screening checklist based on the eligibility criteria. If deemed eligible, a video conference physical screening assessment will be arranged (stage 2). A screening pack will be sent out ahead of this physical screening appointment containing: the screening battery tests (schema of physical tests and instructions), Beighton self-report score, trial consent forms, orthotic measuring guide and tape measure (to capture measurements for production of the customised orthosis, should the participant be allocated to the intervention group) and digital callipers.

The physical screening requires the presence of a partner/trusted other to assist with the physical assessment and orthosis measurements, under the guidance of the remote researcher. All screen failures will be recorded.

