### Randomisation

Once eligibility is confirmed, the consent process completed, and screening data entered into the trial database, participants will be sent a text/email, generated by the Peninsula Clinical Trials Unit (PenCTU), requesting them to complete the baseline questionnaires. Once complete, the participant will be randomly allocated on a 1:1 ratio, using random permuted blocks, stratified by centre and presence/absence of lumbo-pelvic pain pre-pregnancy, to either the standard care or intervention group (figure 1). Screening data capture and randomisation is achieved via a web-based system created by the PenCTU.

After randomisation, a series of emails will be automatically generated. A blinded email will be sent to the research team members involved in eligibility screening. An unblinded email will be sent to the chief investigator (CI), study administrator and site principal investigator (PI). An email/text will be sent to the participant to inform them of their group allocation.

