### Data collection

#### Feasibility outcomes

The trial outcomes include feasibility and acceptability of the EMaPP trial. Quantitative and qualitative feedback will be obtained to identify the main determinants of experience and acceptance of the trial in line with the trial objectives. In particular, the following measures and operational criteria will be determined:

Number and proportion of eligible participants from the target population.Willingness of participants to be randomised.Recruitment and retention rates of eligible participants through the trial.Completeness of data sets/outcome measures.Incidence of face-to-face sessions.

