## Discussion

This is the first RCT to explore the feasibility and acceptability of a novel customised pelvic orthosis in the management of chronic PGP in the postpartum period. There is a lack of evidence to support the management of this condition beyond the first 8 weeks post partum. This orthosis has already shown promise as an intervention during pregnancy,^18^ and in a replicated case series study of eight women post partum.^19^ This trial aims to serve as a starting point to investigate the effectiveness of this orthosis in the management severe chronic PGP post partum.

Some aspects of the study design are noteworthy. All trial procedures and intervention delivery are undertaken remotely; described as a virtual trial.^30 31^ This replicates current practice, mitigates the risk associated with face-to-face appointments during the COVID-19 pandemic and ensures trial delivery in the event of a lockdown. It is also a potentially more efficient approach.^31^ Because some participants may not be able to participate in a fully virtual trial, to optimise generalisability provisions have been made to provide a non-virtual format when this is preferred by the participant. Monitoring of the proportion of women who choose a non-virtual approach will further inform the future trial design.

All outcome measures collected at follow-up time points (apart from adherence to wear time in the intervention group) are patient reported outcome measures (PROMs), and via a web-based application. This approach was chosen on the basis of PPIE input, the rationale being to minimise participant burden. The collection of PROMs minimises the influence of the research team on data collection. Recommendations from Mercieca-Bebber,^32^ have been used to improve PROMS data collection during this trial, such as reducing free-text options in questionnaires, flexible data entry and text/email reminders to enhance data completeness. With regard to wear-time adherence data, this too is collected remotely using the Orthotimer temperature sensor; with the added advantage of providing detailed and objective data which is otherwise challenging to reliably collect via methods such as patient diaries.

The qualitative interviews are also undertaken via remote means. This decision was informed by PPIE discussions, aiming to reduce participant burden in terms of travel time and inconvenience; particularly important considerations for people in pain and looking after young children.

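### The face-to-face option begins only after a video screening with a helper, so it cannot prevent digital exclusion at entry, and its uptake describes only women who could enter virtually

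*Protocol article*

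**What the plan says.** Study settings in the protocol article describes the whole trial as remote: "The trial undertakes a remote, distance-based approach to its delivery at all stages". It lists telephone and virtual screening, and then gives the safeguard: "To prevent digital exclusion, face-to-face intervention will be delivered at a local healthcare establishment when required". The Interventions section applies the same option, at the woman's preference, to the two physiotherapy sessions.

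Eligibility screening process sets out two stages. Stage 1 is a telephone check against the eligibility criteria. For stage 2 it says: "If deemed eligible, a video conference physical screening assessment will be arranged (stage 2". It adds that "The physical screening requires the presence of a partner/trusted other to assist with the physical assessment and orthosis measurements", with the researcher guiding remotely. No in-person alternative is described. The same section says that screen failures are recorded.

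Randomisation gives the order of steps: "Once eligibility is confirmed, the consent process completed, and screening data entered into the trial database, participants will be sent a text/email" asking for the baseline questionnaires, and allocation follows once these are complete. Clinical outcome measures says that women enter all patient-reported measures themselves through the web application.

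Feasibility outcomes lists "Incidence of face-to-face sessions". The Discussion accepts that some women may be unable to join a fully virtual trial, says that a non-virtual format is available on preference to support generalisability, and adds: "Monitoring of the proportion of women who choose a non-virtual approach will further inform the future trial design".

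**The concern.** The safeguard sits after the step at which digital exclusion would first occur. A woman without usable video stops at stage 2 and never reaches the point at which she could choose face-to-face sessions. A woman with good video but no helper stops there too, for a different reason.

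This matters because the trial exists to test its procedures, and the uptake of a non-virtual format is one of the results meant to shape the definitive trial. If that uptake is observed only in women who have already completed an assisted video assessment and web questionnaires, a low figure could be read as little demand for non-virtual delivery when part of the demand was lost before it could be counted. The generalisability statement in the Discussion would then rest on a group selected for virtual access.

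**Working it through.** **Order of steps, as the article gives it**

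| Step | Format stated | Face-to-face alternative stated? |
|---|---|---|
| Stage 1 screen | Telephone | Not needed for video access |
| Stage 2 physical screen and orthosis measurement | Video, helper required, researcher remote | None described |
| Baseline questionnaires | Text/email prompt, web entry | None described |
| Randomisation | Web-based system | Not applicable |
| Two physiotherapy sessions | Video | Yes, on preference or when required |
| Follow-up questionnaires | Web application | None described |

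The option appears in one row only, and that row comes after randomisation. Face-to-face sessions can therefore be counted only among women who passed the video and web steps.

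**Does this bias the uptake figure, and by how much?** The article gives no figure for demand, for losses at stage 2 or for expected uptake, so there is nothing of its own to reproduce on this point. Its retention precision and its 24 followed up per group do not depend on it.

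Three quantities are needed, and all are assumptions:

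- x: share of otherwise eligible women lost at the video or helper step;
- w: share of those lost who would use a face-to-face format;
- m: share choosing face-to-face among women who get through. This is what the trial measures.

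Demand in the target population is N = x·w + (1 − x)·m. The shortfall is N − m = x·(w − m). It is zero if x = 0 or w = m, and measured uptake is too low exactly when x > 0 and w > m. If the women lost wanted face-to-face less often than those who passed, the error would run the other way.

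Illustration, with w from 50% to 100%:

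| x | N if m = 5% | N if m = 10% | N if m = 20% |
|---|---|---|---|
| 0% | 5% | 10% | 20% |
| 5% | 7.25% to 9.75% | 12.0% to 14.5% | 21.5% to 24.0% |
| 10% | 9.5% to 14.5% | 14.0% to 19.0% | 23.0% to 28.0% |
| 20% | 14.0% to 24.0% | 18.0% to 28.0% | 26.0% to 36.0% |

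Worked case: x = 10%, m = 10%, w = 50% gives 0.10 × 0.50 + 0.90 × 0.10 = 0.14. With w = 100% it gives 0.10 + 0.09 = 0.19. The spread shows that the answer is driven by x and w, neither of which the article says will be recorded.

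**The case against.** The strongest reply has five parts.

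- **The safeguard is worded for the intervention.** Study settings speaks of face-to-face intervention, so it does not promise in-person screening. This stands in part. The purpose given is still to prevent digital exclusion, and the Discussion extends the provision to generalisability, which depends on who gets in.
- **The option still works for some women.** A woman may manage one assisted call and yet be unable or unwilling to have treatment by video. This stands. A reader might infer that the option prevents no digital exclusion at all, and the article does not support that.
- **The measure concerns choice, not need.** If the definitive trial keeps the same screening, uptake among women who pass it is a valid planning figure. This also stands, but only for that design. The figure cannot say whether a non-virtual entry route is wanted.
- **Losses may be logged.** Screen failures are recorded, the CONSORT diagram draws on screening logs, and women who did not return the reply slip may be contacted about their reasons. It would go too far to say that these women vanish from the record, since the detailed reason codes may sit in documents not shown. Still, contact with non-responders misses women who replied and then stopped at stage 2, and neither safeguard changes the denominator of the uptake figure.
- **The conditions are not hidden.** They are absent from Table 1, but Eligibility screening process states them openly. Lack of a helper is also a separate access barrier, not digital exclusion.

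Finally, the Discussion's general wording does not exclude a non-virtual screening, and the full protocol may describe one. The article does not, and Study settings and Eligibility screening process point the other way.

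**Conclusion.** The point holds in a limited form. As the article stands, the face-to-face option cannot prevent digital exclusion at entry, and the incidence of face-to-face sessions measures uptake among women already able to enter virtually. It will understate demand in the target population if women lost at the video step want face-to-face more often than those who pass. That is plausible for women without video and uncertain for women who lack only a helper.

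The size is unknown. A reader might infer a multiplier. With w = 100%, x from 5% to 15% and m from 5% to 10%, N/m runs from (0.05 + 0.95 × 0.10)/0.10 = 1.45 to (0.15 + 0.85 × 0.05)/0.05 = 3.85. The documents do not support this as an estimate. All three inputs are assumed, and w = 100% treats every woman lost, including those lacking only a helper, as wanting face-to-face delivery.

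The incidence of face-to-face sessions is not among the progression criteria in Table 3, and the pain comparison among randomised women is not affected. What is affected is what this feasibility trial can conclude about non-virtual provision.

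**What to change.** 1. Reconcile Study settings, Eligibility screening process, Interventions and the Discussion. If a non-virtual screening route exists, state it. If not, limit the digital-exclusion and generalisability statements to delivery of the intervention.
2. At the existing stage 1 telephone call, ask whether the woman can do a video assessment and whether she has someone to help.
3. Record no video access, no helper, and prefers non-virtual as three separate reasons for not proceeding.
4. Report women unable or unwilling to use the virtual format out of all women otherwise eligible at stage 1, with lack of a helper shown separately. Put this beside face-to-face uptake among randomised women. Do not pool the two: women who stop before stage 2 have not had the physical tests, so some would have proved ineligible.

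The cost is two questions, three reason codes and one further denominator, with no extra visits. The trial is still recruiting, so the items can be collected from here on. The drawbacks are that women already screened will lack them, so the stage 1 figure covers only part of the screened group, and that the reported need for non-virtual provision may be higher.
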